### Clinical Study CT Scans

After the radiopaque markers have been applied to the residual limb and liner, the socket with embedded brass beads will be donned by the participant and a single CT scan of the residual knee joint and tibia will be acquired while participants lie in the supine position with their socket and liner on and with the knee extended. CT scans provide gray-scale volumes for use with DSX and high-resolution 3D surface models required for computing all outcome variables. CT volume images will be acquired at a resolution of 512×512×0.625 mm^3^ (120 kVp; SMART mA). Surface3D (C-Motion Inc) will be used to segment 3D models of the socket, liner, and tibia from the CT volumes.

### Quantification of the Relative Motion Between the Residual Bone and the Prosthetic Socket

Quantification of the 3D position and orientation of the residual limb has been previously described in detail [23]. In brief, the residual tibia will be tracked throughout the gait cycle, with the coordinate system defined in the CT space using a morphology-based coordinate systems adapted from previous studies [37,38]. These coordinate systems will be registered between Visual3D (C-Motion, Inc) and CT space using the coregistration transformation matrix. The position and orientation (pose) of the socket will also be tracked with 2-mm brass beads secured to the exterior of the prosthetic socket. To provide a context for the relative motion of the residual tibia and socket, 3D infrared motion capture will synchronously be recorded with the DSX data for each participant. Anatomical frames of the thorax, pelvis, and thigh will be constructed by placing retroreflective markers on anatomical locations. Visual3D will be used to establish the anatomical reference frames, estimate the position and orientation of all segments, and compute the kinematics. The reference frames for the socket will be established based on the sagittal plane of the prosthesis. The sagittal plane will be defined by the long axis of the foot. The axial direction will be defined by the pylon. The lateral direction will be perpendicular to the sagittal plane. The anterior direction will be the cross-product of the axial and lateral directions.

To use the same reference frames for both imaging techniques, the global coordinate systems of the optical motion capture and DSX systems will be coregistered by simultaneously capturing the static position of a rigid lattice consisting of 11 radiopaque, spherical markers outfitted with retroreflective tape. The transformation matrix for the coregistration of each global coordinate space will be computed and applied to the respective kinematic data sets. The pose of the socket will be estimated using a standard 6-DOF pose estimation with a set of beads as tracking markers implanted into the socket. The socket reference frame will be established by structural landmarks on the prosthesis in the CT image.

### Data Processing

Validation of DSX systems for 3D volumetric model-based tracking has been previously reported [39-41]. For each participant, the residual tibia will be segmented from the CT volume to construct a polygonal mesh of the tibia surface. Digitally reconstructed radiographs (DRRs) created from participant-specific CT scans will be matched to the DSX images in the inline and offset views to calculate the 3D pose of the tibia (Figure 5) [18,41]. DRRs will be generated by positioning the segmented CT volume within a virtual x-ray system and projecting rays through it to create a simulated x-ray image [23]. The optimal position and orientation of the bone will be defined as the pose that maximizes the similarity between the pair of DRR images and their corresponding x-ray images. To track each trial, the tibia will first be manually positioned in every fourth frame of data. Subsequently, a cubic spline will be fitted to the set of manual positions and orientations of the bone, which can be interpolated by the model-based tracking algorithm to determine a pose of the bone in every frame.

**Figure 5 figure5:**
[figure not shown]
A 3D representation of the synchronized x-rays. The inline x-ray image is the red frame (A), whereas the offset x-ray image is the green frame (B). The 3D residual tibia (C) is reconstructed from computed tomography (CT) data. The red and green lines are the perpendiculars from the x-ray image planes to the x-ray sources. The outlines of the tibia (shown in yellow) superimposed over each x-ray image are created by casting rays from each x-ray source through the CT tibia to the x-ray planes.

The algorithm output will be a set of 4×4 transformation matrices representing the pose of the residual tibia. The position and orientation of the socket will be calculated using beads placed on the rigid socket for each time frame. Excursions for relative tibial rotations and translations will be defined as the difference between the maximum and minimum values for each variable within the gait cycle. The differences between the residual bone movement with the EV and traditional suction will be determined in 6 DOF for each participant. Group differences for tibial rotations and translations will be compared at initial contact, toe-off, and swing phase as well as for the total excursions of the residual tibia during the gait cycle.

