### Study Objectives and Aims

There remains an unmet need to fill the gap of accurate, biomechanical evaluations of residual limb-socket kinematics, which can then be effectively translated into evidence-based clinical practice. Furthermore, quantifying dynamic shear and tissue deformation is yet to be efficiently evaluated to determine the exact mechanism of tissue strain. Therefore, the objective of this investigation is to develop quantitative, dynamic analytical tools to quantify both 3D bone movement as well as soft tissue and liner deformation at the socket-residual limb interface for individuals with transtibial limb loss. To meet the study objective, the following aims will be addressed: (1) to optimize the DSX procedural setup for the accurate tracking of the prosthetic socket, skeletal kinematics, and tissue and liner deformation; (2) to quantify the relative motion between the residual tibia and the prosthetic socket during dynamic activities; and (3) to measure the deformation of the skin and liner in the prosthetic socket during dynamic activities. The proposed investigation will use a state-of-the-art DSX system to accurately quantify 3D in vivo residual limb-socket kinematics during dynamic activities. To verify the sensitivity of this technique and its relevance to individuals with transtibial limb loss, residual limb-socket kinematics will be evaluated in 2 different socket suspension systems: elevated vacuum (EV) and traditional suction. It is hypothesized that an efficient and highly accurate method to quantify the dynamic interaction between the residual limb and the prosthetic socket will be sensitive enough to distinguish between different types of prosthetic socket suspension systems, which will further enhance the biomechanical understanding of residual limb-socket kinematics.

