### Deformation of the Skin

Deformation of the skin will be evaluated in the same way as in the cadaver experiments. In brief, 2 primary metrics will be used to quantify skin deformation: shear and compression. For shear, the end points from the lines will be digitized and the 3D trajectories will be used to reconstruct the 3D shape of the line at each time frame. The angles between the lines will be measured in the static pose to quantify the baseline skin shear. The change in angle will be measured during each dynamic task. Shear will be measured as the change in angle relative to the angle in the static position. Compression will be calculated by the change in distance between lines as well as a neutral position. As with shear, baseline distances will be calculated from the static trial.

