#### Power Analysis

Table 1 outlines the sample size estimate required to achieve 90% power for the key variables of interest. A previous pilot investigation for individuals with transfemoral limb loss [23] indicated an effect size of 0.77 for residual femur axial translation. Assuming an α of .05, using paired *t* tests, 21 participants are required to achieve 90% power to detect a 0.5 cm difference in axial translation. Owing to the paucity of highly accurate data on movement between the residual tibia and socket, data from Board et al [1] were used to calculate an effect size for tibia translation (1.75) for suction and EV suspension. Given an effect size of 1.75 and an α of .05 for a paired *t* test, a sample size of 21 will be powered at >99% to detect differences between EV on and off. For skin strain, Gale et al [30] found a maximum shear strain of approximately 0.08. Assuming a shear strain of 0.08 with a moderate effect size of 0.75 (α=.05), a sample size of 21 will be required to achieve 90% power to detect differences between EV on and off.

**Table 1 table1:** Power analysis.

Measure	Values, mean (SD)	Sample size for achieving 90% power, n
Femur distal translation (cm)	2.0 (0.6)	21
Tibial translation (cm)	4.0 (0.4)	6
Skin shear strain	0.08 (0.02)	21

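### No primary outcome or success criterion is fixed for the suspension comparison, although roughly 54 to 72 bone-motion comparisons plus skin and liner tests are planned

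*Protocol article*

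**What the plan says.** - **Hypothesis (Study Objectives and Aims).** The method is expected to be "sensitive enough to distinguish between different types of prosthetic socket suspension systems". The hypothesis names no variable, activity, time point or criterion for success.
- **Bone motion (Data Processing, text below Figure 5).** "Group differences for tibial rotations and translations will be compared at initial contact, toe-off, and swing phase as well as for the total excursions". The comparison is made in 6 DOF. The Bone Movements section assigns paired t tests to it.
- **Activities (DSX Experimental Design).** Walking at self-selected speed, walking 10% faster, and a step-down.
- **Skin and liner.** Deformation of the Skin says "2 primary metrics will be used to quantify skin deformation: shear and compression". That makes them the main measures of deformation, not primary outcomes of the trial. Skin and Liner Deformation repeats the paired t tests for marked regions whose number is still to be settled by the cadaver work.
- **Sample size (Power Analysis).** "Table 1 outlines the sample size estimate required to achieve 90% power for the key variables of interest". The table lists femur distal translation, tibial translation and skin shear strain, unranked. Each is planned as a single paired test at .05. The first is a transfemoral measure that this transtibial study does not collect.

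**The concern.** The article states a hypothesis to be tested and sizes the study for single tests at .05, but never says which result answers the hypothesis. With dozens of candidate results and none given priority, a reader cannot tell beforehand what would count as support and what would count against it. If EV had no effect on any outcome, a few nominally significant differences would still be unsurprising, and any of them could be presented as evidence that dynamic stereo x-ray is sensitive to suspension type. The 90% power claim also loses its meaning when the powered variables have no special standing in the analysis.

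**Working it through.** **1. The plan's own sample sizes.** Inputs from Power Analysis: "Assuming an α of .05"; the pilot "indicated an effect size of 0.77 for residual femur axial translation"; effect size 1.75 for tibial translation; 0.75 for skin shear. Exact paired-t power is 1 − F(t₀.₉₇₅,ₙ₋₁) + F(−t₀.₉₇₅,ₙ₋₁), where F is the noncentral t distribution with n − 1 degrees of freedom and noncentrality d√n. At n = 21:

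- d = 0.77: noncentrality 0.77 × √21 = 3.53, power 91.8%. The smallest n for 90% is 20. The article says "21 participants are required to achieve 90% power to detect a 0.5 cm difference in axial translation".
- d = 0.75: noncentrality 3.44, power 90.5%. The smallest n is 21 (article: 21).
- d = 1.75: noncentrality 8.02, power above 99.9%. The smallest n is 6 (article: 6, and "a sample size of 21 will be powered at >99% to detect differences between EV on and off").

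The stated sizes are reproduced to within one participant with two-sided tests. One-sided tests would give 16, 17 and 5. The planning is therefore for single two-sided tests at .05.

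**2. Number of bone-motion comparisons.** The article gives no count, so it is built from the stated elements.

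- All elements crossed: 6 DOF × 4 summaries (initial contact, toe-off, swing, excursion) × 3 activities = 72.
- Gait events for the two walking tasks only, excursion alone for the step-down: 6 × 4 × 2 + 6 = 54.
- Excursions only: 6 × 3 = 18.

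Skin and liner tests (shear and compression, by region and task) come on top and cannot be counted.

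**3. Chance of at least one p < .05 when EV has no effect, if .05 is used unadjusted.** For k independent tests this is 1 − 0.95^k:

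- k = 72: 1 − 0.95^72 = 97.5%, with 72 × .05 = 3.6 false positives expected.
- k = 54: 93.7%, with 2.7 expected.
- k = 18: 60.3%, with 0.9 expected.

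The documents give no correlation between outcomes, so a range is assumed. Each participant's difference on outcome j is simulated as √ρ·g + √(1−ρ)·eⱼ, where g is shared across outcomes, both terms are standard normal, and n = 21. A two-sided t test is applied to each outcome, with 10,000 replicates:

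| Common correlation (assumed) | 18 tests | 54 tests | 72 tests |
|---|---|---|---|
| 0 (formula) | 60% | 94% | 97.5% |
| .3 | 51% | 83% | 90% |
| .5 | 42% | 66% | 73% |
| .7 | 29% | 43% | 48% |
| .8 | 23% | 32% | 35% |
| .9 | 16% | 21% | 21% |

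If the six DOFs are instead independent of each other and correlated only within a DOF (.5 to .95), the figures are 91% to 50% for 72 tests and 86% to 47% for 54.

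**4. What 21 participants can support.** One test at .05 keeps the power shown in step 1. Bonferroni adjustment lowers it as follows:

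| Tests adjusted for | d = 0.77 | d = 0.75 |
|---|---|---|
| 3 | 81% | 79% |
| 54 | 40% | 37% |
| 72 | 36% | 33% |

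At d = 1.75, power stays above 99.9% even at .05/72.

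**The case against.** Several points on the other side are sound.

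- **Significance level.** The .05 appears only in the sample-size section. The analysis sections set no threshold, and a multiplicity procedure may sit in an analysis plan that is not at hand. The absence of such a procedure is therefore not part of this point, and the error rates above are conditional on unadjusted .05.
- **The count.** The article does not say that 72 tests will be run. The listed events belong to the gait cycle and do not clearly apply to a step-down. Only stance capture is guaranteed (DSX Experimental Design), so swing comparisons may fall away. A hierarchical linear model is assigned to range of motion and to the effect of rate across activities. Seventy-two is the upper end.
- **The decision rule.** A reader might infer that one significant result anywhere would count as success. The article adopts no such rule; it simply states none.
- **Likelihood.** A reader might also infer that chance confirmation is likely. That requires no EV effect and low to moderate correlation. Outcomes from one limb and one stride, at speeds 10% apart, may be highly correlated, and at .9 the risk is about 21%. If the planned tibial effect of 1.75 is real, a positive result would reflect that effect and would survive even Bonferroni over 72.
- **Purpose.** The study mainly develops measurement tools, and much of the 6-DOF reporting is descriptive.

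These points limit the size of the problem but do not remove it. Choosing a primary outcome belongs in the protocol, and the article presents a hypothesis and a power calculation without one. A correction added later would not say which result answers the hypothesis.

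**Conclusion.** The point holds in this form: no primary outcome is named, three key variables are planned unranked at .05 each, and the sensitivity hypothesis has no variable, task or success criterion. Meanwhile roughly 54 to 72 bone-motion comparisons, or 18 on the narrowest reading, and an open number of skin and liner tests are foreseen. With unadjusted .05 testing and no EV effect, the bone-motion tests alone carry a familywise risk above 5% in every case examined, from 16% (18 tests, correlation .9) to 97.5% (72 independent tests). The hypothesis could thus be read as confirmed by chance; the documents do not show that it will be. The figures rest on the assumed test level, count and correlation. The missing primary outcome and success criterion do not depend on those assumptions.

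**What to change.** Before the full-data analysis, name one primary outcome by variable, summary and task. Tibial axial translation excursion relative to the socket, at self-selected walking speed, is the closest match to the translation variables in Power Analysis. That section specifies neither excursion nor speed, so both must be written in. Test it at two-sided .05 and tie the hypothesis in Study Objectives and Aims to that test alone. Optionally, test skin shear second in fixed sequence, with region and task also named. Report all other DOFs, gait events, tasks and regions as secondary or exploratory, with 95% confidence intervals. If the full protocol or the registration already names a primary outcome, carry it into the article and align Power Analysis with it.

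The cost is about a paragraph, with no added data or participants. The Results section places analysis of the full data set after final data collection, so the choice can be recorded in time. The downside is that a striking difference in another DOF or task could be reported only as exploratory.

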### Quantification of Skin and Liner Deformation

Motion between the bone and the skin (skin deformation) and motion between the skin and the inner surface of the liner will be examined simultaneously with bone movement in the prosthetic socket. Motion between these interfaces can be directly associated with discomfort while wearing a prosthesis [3,30]. In addition, motion between the socket and both the skin and inner surface of the liner will be examined for a complete understanding of the motion between the limb and the prosthesis.

The results from the cadaver experiments will inform the final placement of markers on the liner and skin. The final number, sizes, shapes, and placement of markers will be based on the results of the cadaver experiments and any potential overlap or bone occlusion. However, the proposed shapes will make identification of the markers in the x-ray images easier and will foster the ability to examine both shear and compression. The ends of each line will be digitized manually from the 2 sets of x-ray images. Reconstruction of the 3D trajectories of the markers will be performed using the DSX software (C-Motion Inc). Visual3D will be used to estimate the deformation of the skin and liner from the relative movement of the markers in the socket reference frame.

### Motion of the Skin and Interior of the Liner Relative to the Socket and Residual Tibia

The ends of the lines on the skin and liner will be tracked during the dynamic trials, and their trajectories in the socket coordinate system will define the motion of the skin and liner relative to the socket. Their positions in the socket coordinate system during the static trial will serve as the baseline positions. Visual3D contains the tools to define the socket coordinate system and track the motion of the skin markers within this reference frame. The motion of the lines will also be calculated in the coordinate system of the residual tibia. Their positions in the tibia coordinate system during the stationary trial will serve as their baseline positions. The tibia coordinate system will be defined to track the motion of the skin and liner markers within this reference frame.

### Deformation of the Skin

Deformation of the skin will be evaluated in the same way as in the cadaver experiments. In brief, 2 primary metrics will be used to quantify skin deformation: shear and compression. For shear, the end points from the lines will be digitized and the 3D trajectories will be used to reconstruct the 3D shape of the line at each time frame. The angles between the lines will be measured in the static pose to quantify the baseline skin shear. The change in angle will be measured during each dynamic task. Shear will be measured as the change in angle relative to the angle in the static position. Compression will be calculated by the change in distance between lines as well as a neutral position. As with shear, baseline distances will be calculated from the static trial.

### Data and Statistical Analysis

#### Overview

Descriptive statistics will be used to summarize demographic and continuous baseline variables. Median and IQR will be used to classify nonnormal or ordinal data. For the clinical experiment, a between-participant factor at 2 levels (EV on and EV off) will be used. The interaction of the suspension condition (EV on or off) will determine the efficacy of the EV system on the outcome measures.

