### DSX Experimental Design

Following the 4-week acclimation period, the participants will be evaluated at the Rutgers New Jersey Medical School DSX facility. To evaluate the 6 DOF kinematics of the residual limb within the socket, participants will separately walk on a treadmill at a self-selected speed, at a speed 10% faster, and during a step-down task from an 18 cm–high platform. The DSX system will be oriented such that all tasks can be recorded with the same configuration. These movement tasks will be completed under 2 conditions: with the EV suspension active and with the EV system inactive (traditional suction). For testing with the traditional suction suspension (EV inactive), the vacuum connector will be replaced with a PushValve (Ottobock, Inc) [11]. A randomized block, crossover design will be used to evaluate the residual limb-socket fit. A group of 11 participants (group 1) and a group of 10 participants (group 2) will be formed. Participants in group 1 will first be tested in the DSX system with the EV on, and then, they will repeat all procedures with the EV inactive. Participants in group 2 will first be tested in the DSX system with the EV inactive, and then, they will repeat the tasks with the EV active. After each suspension method is applied, participants will be instructed to perform normal daily activities for 2 hours to allow for acclimation and for transient changes (eg, volume loss) to manifest. A period of 2 hours was chosen so that both conditions can be tested on the same day while still capturing 90% of the volume loss during socket use [1]. Up to 4 trials of DSX will be conducted for each task for each socket condition, giving a maximum of 24 trials per participant. For each task, DSX data will be collected and analyzed to determine the underlying bone movement and skin strain with respect to the socket. Separate CT scans of the residual limb and socket will also be captured for each participant to generate participant-specific socket and bone models of the residual limb for tracking kinematics.

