#### Bone Movements

The differences between the residual bone movement with the EV and the traditional suction suspension will be determined in 6 DOF for each participant. Briefly, group differences for tibial rotations and translations as well as total excursions of the bone for each suspension condition will be compared during the gait cycle. Paired *t* tests will be performed and a between-participant factor at 2 levels (EV on and EV off) will be used. A hierarchical linear model will be used to evaluate the tibial range of motion (ie, maximum translation and rotation) as a function of tibial position and potential confounding factors (eg, gender, age, etiology, and time since limb loss). The hierarchical linear model will also be used to evaluate the tibial motion path and the effect of rate during the 3 different activities.

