#### Skin and Liner Deformation

The characterization of 3D skin deformation will be performed by comparing the 3D position of the skin markers at rest, or unloaded position, to the 3D positions of the markers when deformed during each task to produce relative strain assessments for marked regions of the residual limb. The characterization of 3D deformation will be measured between the suspension methods. Paired *t* tests will be performed as previously described for bone movements. Linear regression models will be used to evaluate the potential confounding factors.

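### EV on/off is labelled a between-participant factor, and efficacy is tied to an interaction with no second factor, contradicting the crossover, the paired tests and the paired power calculation

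*Protocol article*

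**What the plan says.** **Design.** Under DSX Experimental Design: "A randomized block, crossover design will be used to evaluate the residual limb-socket fit". Group 1 is tested with EV on, after which "they will repeat all procedures with the EV inactive"; group 2 does the reverse. The two groups differ only in order: "A group of 11 participants (group 1) and a group of 10 participants (group 2) will be formed". Prosthetic Suspensions also has every participant tested in both conditions, in counterbalanced order.

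**Analysis.**
- The Overview of Data and Statistical Analysis says that "a between-participant factor at 2 levels (EV on and EV off) will be used" and that "The interaction of the suspension condition (EV on or off) will determine the efficacy of the EV system on the outcome measures".
- Bone Movements repeats the label beside a paired test: "Paired *t* tests will be performed and a between-participant factor at 2 levels (EV on and EV off) will be used". It adds a hierarchical linear model with potential confounders.
- Skin and Liner Deformation says: "Paired *t* tests will be performed as previously described for bone movements". It adds linear regression models for confounders.

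**Power.** The Power Analysis section states: "using paired *t* tests, 21 participants are required to achieve 90% power to detect a 0.5 cm difference in axial translation". It also uses a paired t test for tibial translation.

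**The concern.** Two statements are wrong as they stand.

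1. In a crossover where each person supplies a value under EV and a value under suction, suspension varies within the person. Calling it between-participant places person-to-person variation (anatomy, limb length, own ankle-foot device) in the error term, which the crossover is meant to remove. It also cannot be reconciled with a paired t test on the same two levels.
2. An interaction needs two factors, and only suspension is named. The second could be activity, test order or a participant characteristic. Each would answer a different question, and none is the average EV-minus-suction difference for which the trial is powered. The sentence that says what decides efficacy therefore leaves the deciding contrast undefined.

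The risk lies where the paired t test does not settle the matter. Neither the hierarchical model nor the regression models are said to treat suspension as a repeated factor. The patient surveys are completed once per suspension method and have no named test, so the Overview wording is the only guidance that reaches them.

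**Working it through.** **Step 1: what kind of factor is suspension?**

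| Place | What it implies |
|---|---|
| Prosthetic Suspensions; DSX Experimental Design | within participant: each person tested in both states |
| Data Processing; Bone Movements | within participant: differences determined for each participant |
| Bone Movements; Skin and Liner Deformation | within participant: paired t tests |
| Power Analysis | within participant: paired t test for femur and tibial translation |
| Overview; Bone Movements | between participant, by label |

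The label is the outlier.

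**Step 2: reproduce the plan's own figures.** Inputs from Power Analysis: α = 0.05, n = 21, and effect sizes d = 0.77 (femur axial translation), 0.75 (skin shear strain) and 1.75 (tibial translation). A two-sided test is assumed because the article does not state sidedness.

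For a paired t test, power is the probability that |T| exceeds t(0.975; n − 1), where T is noncentral t with n − 1 degrees of freedom and noncentrality d√n.

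| d | d√21 | Power at n = 21 | Smallest n for 90% | n in Table 1 |
|---|---|---|---|---|
| 0.77 | 3.53 | 91.8% | 20 | 21 |
| 0.75 | 3.44 | 90.5% | 21 | 21 |
| 1.75 | 8.02 | >99.9% | 6 | 6 |

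The stated sizes are reproduced (within one for 0.77). They are paired figures, including skin shear strain, for which the text names no test.

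**Step 3: what if the between-participant wording were followed?** Treat the 21 EV and 21 suction values as two independent samples. Let ρ be the within-person correlation, which the article does not give. The paired effect size divides the mean difference by the SD of the differences, and that SD equals σ√(2(1 − ρ)). The difference in units of σ is therefore

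d_between = d × √(2(1 − ρ)).

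For d = 0.75 this gives 0.75 × √2 = 1.061 at ρ = 0; 0.75 × √1.4 = 0.887 at 0.3; 0.75 × 1 = 0.75 at 0.5; and 0.75 × √0.4 = 0.474 at 0.8.

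The textbook two-sample power for these values is not the rate at which the test would reject, because the pairs are correlated. The rejection rate was therefore simulated: correlated normal pairs, n = 21, unpaired t test with 40 degrees of freedom, 1,000,000 trials per cell.

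| ρ (assumed) | d = 0.75, two-sample formula | d = 0.75, simulated | d = 0.77, simulated | d = 1.75, simulated |
|---|---|---|---|---|
| 0 | 92% | 92% | 93% | >99% |
| 0.3 | 80% | 84% | 86% | >99% |
| 0.5 | 66% | 71% | 74% | >99% |
| 0.8 | 32% | 19% | 21% | >99% |

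At ρ = 0 nothing is lost. The loss grows with ρ for the two smaller effect sizes. Tibial translation is hardly affected over this range.

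**The case against.** The strongest reply is that the plan names one test for the EV comparison, the paired t test, for both bone movement and deformation. It also forms differences within each participant and bases its translation power on paired tests. No section prescribes an independent-samples test, and a hierarchical model is itself a usual tool for repeated measurements. On this view the label is a slip in a condensed article, and an analyst would run the right test anyway.

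Much of this stands. A reader might infer that the analysis as written forfeits the stated 90% power. The documents do not support that, because the named tests deliver 90.5% to 91.8%. The loss in Step 3 is conditional on following the label instead of the named test, and on a correlation that must be assumed. The tibial comparison, which concerns the bone studied here, would be almost untouched.

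A reader might also infer that test order is the only between-participant factor, or that suspension by activity must be the interaction meant. Neither follows. Bone Movements lists gender, age, etiology and time since limb loss, all of which differ between people, and nothing identifies the second factor.

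The reply does not remove the contradiction. The label appears twice with its levels spelled out. The paired t tests do not repair the interaction sentence, which is the article's only statement of what determines efficacy. They also do not govern the hierarchical and regression models.

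**Conclusion.** The point holds as an internal contradiction and an undefined efficacy contrast; it should be fixed. Suspension is within-participant by design, and the label and the interaction sentence conflict with the design, the named tests and the power calculation. This conclusion needs no numerical assumption.

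The size is conditional. With the named paired tests there is no loss of power. If the label were followed, an outcome with effect size 0.75 would fall from 90.5% to roughly 84%, 71% or 19% at correlations of 0.3, 0.5 or 0.8, with no loss at 0. These figures assume two-sided testing, normal data, equal variances and the plan's effect sizes read as paired ones, a reading that its sample sizes confirm.

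**What to change.** 1. In the Overview and in Bone Movements, call suspension (EV on, EV off) a within-participant, repeated factor. Say that this also applies in the hierarchical linear model and in the regression models for deformation.
2. Replace the interaction sentence with: the efficacy of EV is the within-participant EV-minus-suction difference (main effect of suspension), reported with a 95% CI.
3. If an interaction is intended, name its second factor and present it as a separate, secondary question. The choice is the sponsor's.

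The cost is a wording change in the protocol and any SAP. Sample size, data collection and the paired t tests are unaffected. The Results section says that analysis of the full data set starts after final data collection, so the change should be recorded before then.
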